## Abstract

**Introduction:**

The main surgical dilemma during glioma resections is the surgeon’s inability to accurately identify eloquent areas when the patient is under general anaesthesia without mapping techniques. Intraoperative stimulation mapping (ISM) techniques can be used to maximise extent of resection in eloquent areas yet simultaneously minimise the risk of postoperative neurological deficits. ISM has been widely implemented for low-grade glioma resections backed with ample scientific evidence, but this is not yet the case for high-grade glioma (HGG) resections. Therefore, ISM could thus be of important value in HGG surgery to improve both surgical and clinical outcomes.

**Methods and analysis:**

This study is an international, multicenter, prospective three-arm cohort study of observational nature. Consecutive HGG patients will be operated with awake mapping, asleep mapping or no mapping with a 1:1:1 ratio. Primary endpoints are: (1) proportion of patients with National Institute of Health Stroke Scale deterioration at 6 weeks, 3 months and 6 months after surgery and (2) residual tumour volume of the contrast-enhancing and non-contrast-enhancing part as assessed by a neuroradiologist on postoperative contrast MRI scans. Secondary endpoints are: (1) overall survival and (2) progression-free survival at 12 months after surgery; (3) oncofunctional outcome and (4) frequency and severity of serious adverse events in each arm. Total duration of the study is 5 years. Patient inclusion is 4 years, follow-up is 1 year.

**Ethics and dissemination:**

The study has been approved by the Medical Ethics Committee (METC Zuid-West Holland/Erasmus Medical Center; MEC-2020–0812). The results will be published in peer-reviewed academic journals and disseminated to patient organisations and media.

**Trial registration number:**

ClinicalTrials.gov ID number NCT04708171 (PROGRAM-study), NCT03861299 (SAFE-trial)

Strengths and limitations of this studyFirst multicentre prospective study directly comparing awake mapping, asleep mapping and no mapping for glioblastoma resections in or near eloquent areas.International, multicenter design on a large scale, which will be of substantial benefit with regard to subgroup analyses and external generalisability of the results.Observational design will not exclude all possible, inherent forms of bias.

## Introduction

Gliomas are the most common malignant tumours of the central nervous system and are classified into grades 1–4, where grades 1 and 2 consist of low-grade gliomas (LGG) and grades 3 and 4 represent high-grade gliomas (HGG).^1 2^ Gliomas are relatively rare (incidence of 5/100 000 persons/year in Europe and North America), but are associated with a relatively high morbidity and mortality regardless of years of scientific efforts to improve clinical outcomes in these patients.^1–7^

Studies show that maximising the extent of resection of the contrast-enhancing part—and recently, the non-contrast-enhancing part as well—results in improved patient survival rates.^8–15^ Moreover, patients with gross-total resections derived the most benefit from the adjuvant chemoradiotherapy compared with patient with subtotal resections.^16^ However, in excess of 50% of gliomas are located in or near eloquent areas of the brain.^2^ Eloquent areas are important areas within the brain where speech and/or motor functions are located. Damaging these areas during surgery can lead to severe and permanent neurological deficits that seriously impact the quality of life. As a consequence of this worsened condition, some patients are excluded for radiotherapy and chemotherapy, leading to suboptimal clinical outcomes.^16^

Thus, the main surgical problem for the surgeon is the inability to accurately identify these eloquent areas when the patient is under general anaesthesia (GA) when no brain mapping techniques are being used. Surgeons often choose a more defensive approach for tumours that are located in or near these areas to prevent postoperative neurological deficits in patients with an already poor prognosis.^2 10 12–15^ The use of intraoperative stimulation (neurophysiological) mapping techniques (ISM) can be necessary to enable the surgeon to resect as much tumour as possible while preserving quality of life and neurological functioning in these patients.^17^ Mapping of motor-eloquent tumours can be performed while the patient is awake or asleep, while speech mapping can only be performed when the patient is awake. The use of mapping techniques has tremendous potential in glioma resections in eloquent areas, especially for HGG patients. However, there is currently no international consensus regarding the use of these techniques. The scientific evidence for the use of these techniques in this patient group is currently both inconclusive and fragmented. We therefore propose an international, multicenter prospective cohort study in which the use of awake and asleep mapping techniques in HGG patients will be evaluated.

The described research initiative will be able to study these techniques in a prospective setting while covering a breadth of centres and countries. Hence, the data generated in this ENCRAM (The European and North American Consortium and Registry for Intraoperative Stimulation Mapping) research collaboration will be able to answer multiple research questions with excellent generalisability, external validity and overall quality in both a cost-effective and practical setting.^18^

## Methods and analysis

### Study design

This is a international, multicenter, prospective, three-arm cohort study. Eligible patients are operated using awake mapping, asleep mapping or no mapping with a 1:1:1 ratio with a sequential computer-generated random number as subject ID. Patients with motor-eloquent tumours will be treated in all study arms, while speech-eloquent tumours will only be treated in either the awake mapping or no mapping arm. The PROGRAM study (prospective cohort study of high-grade glioma resections using awake craniotomy and intraoperative stimulation mapping) is similar to the SAFE-trial (SAFE surgery for glioblastoma patients: awake craniotomy versus craniotomy under general anesthesia: a multicenter randomized controlled trial) and is initiated by the same center, however, the presented study will be different in various ways: the PROGRAM study (1) will be an observational, prospective cohort study, (2) will include asleep mapping as an additional treatment arm, (3) will evaluate the extent of resection of the non-contrast-enhancing part of the tumour as well, (4) will include both WHO grade III and grade IV gliomas, (5) will include an oncofunctional score as one of the outcomes and (6) will include neurosurgical centers in the USA and is part of the ENCRAM Research Consortium.^18^

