### Sample size

This study has two primary endpoints. In order to guarantee that the overall type I error rate does not exceed 5%, we apply a weighted Bonferroni correction for multiple testing. The sample size calculations that follow take that into account. For the first primary endpoint, proportion of patients with neurological deterioration at 6 weeks postsurgery, we assume a deterioration rate of 10% in the control group (arm 3: no mapping), and 3% in the experimental groups (arm 1 and 2: awake and asleep mapping). A two-sample test for proportions with continuity correction requires 411 patients (137 per arm) in total in order to detect the above-mentioned difference of 7% with 80% power at a 4% significance level. For the second primary endpoint, proportion of patients without residual contrast-enhancing tumour on postoperative MRI, we assume a success rate of 25% in the control group (arm 3: no mapping), and 50% in the experimental groups (arm 1 and 2: awake and asleep mapping). A two-sample test for proportions with continuity correction requires 188 patients (94 per arm) in total in order to detect the above-mentioned difference of 25% with 80% power at a 1% significance level. In order to power the study for both primary endpoints, we should include the larger required number of patients, that is, 411. A total of 411 eligible and evaluable patients in three arms allow the difference of 25% in proportion of patients without residual tumour to be detected with 88% power. Taking into account possible ineligibility and withdrawal of consent (we estimate this at 10%), a total of 453 patients will be included (151 patients per arm).

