### Data collection

All patient data are collected using the electronic data software Castor EDC (Electronic Data Capture). This software allows built-in logical checks and validations to promote data quality. Data entry and group allocation is performed by the study coordinator or locally by trained physicians and research nurses under supervision of the local investigator.

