### Study monitoring

No scheduled on-site monitoring visits will be performed. Local investigators will remain responsible for the fact that the rights and well-being of patients are protected, the reported trial data are accurate, complete and verifiable from source documents and the conduct of the trial is in compliance with the currently approved protocol/amendment(s), with GCP (Good Clinical Practice) and with the applicable regulatory requirement(s). Direct access to source documentation (medical records) must be allowed for the purpose of verifying that the data recorded in the CRF are consistent with the original source data. No data safety monitoring board will be installed: all interventions are care-as-usual and patients are allocated without randomisation.

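### The stated 1:1:1 ratio cannot be guaranteed alongside consecutive enrolment and unrandomised usual care, and nothing in the protocol says how it would be reached

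*Protocol article*

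**What the plan says.** **The ratio.** The abstract (Methods and analysis) states: "Consecutive HGG patients will be operated with awake mapping, asleep mapping or no mapping with a 1:1:1 ratio". Study design repeats the ratio for eligible patients, who are "operated using awake mapping, asleep mapping or no mapping with a 1:1:1 ratio". Sample size builds on it: the calculation "requires 411 patients (137 per arm) in total", and after an allowance for ineligibility and withdrawal "a total of 453 patients will be included (151 patients per arm".

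**How patients come to an arm.** Study design says the study "will be an observational, prospective cohort study". Study monitoring says "all interventions are care-as-usual and patients are allocated without randomisation", and gives this as the reason for having no data safety monitoring board. The surgery case report form records the surgeon's reason for the modality used. The computer-generated random number is described only as a subject ID.

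**Restriction on one arm.** Study design also says "speech-eloquent tumours will only be treated in either the awake mapping or no mapping arm".

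**Wording that suggests allocation.** Data collection says "Data entry and group allocation is performed by the study coordinator or locally by trained physicians and research nurses". Participant timeline speaks of patients being allocated to a group. The analysis sections adjust for minimisation factors, although no minimisation is described. The article gives no allocation procedure, arm quota or arm-closure rule.

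**The concern.** A fixed ratio belongs to a design in which the study controls assignment. Here the surgeon's usual practice sets the technique, so the split among consecutive patients is whatever practice produces. A site that read the ratio as an instruction would have to act on it, and each way of acting does harm:

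- **Influencing the technique** departs from care as usual and removes the reason given for having no data safety monitoring board.
- **Closing an arm when full** ends consecutive enrolment and places the arms partly in different calendar periods, so that an arm effect is partly a period effect.
- **Choosing centres by technique** ties arm to centre, so that an arm effect is partly a centre effect.

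The restriction on speech-eloquent tumours makes equal arms less likely to arise unaided, because only part of the population can fill the asleep arm.

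**Working it through.** **1. The plan's own figure.** Inputs from Sample size: 10% versus 3%, 80% power, 4% significance, continuity correction. Sidedness is not stated. The stated 137 per arm reproduces as a one-sided test of no mapping against both mapping arms pooled (ratio r = 2):

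- Pooled rate = (0.10 + 2 × 0.03)/3 = 0.0533.
- Uncorrected n = [1.751 × √(1.5 × 0.0533 × 0.9467) + 0.842 × √(0.09 + 0.0291/2)]² / 0.07² ≈ 116.
- Continuity-corrected n = (116/4) × [1 + √(1 + 6/(2 × 116 × 0.07))]² ≈ 136.6, so 137 controls and 274 mapped, 411 in total.

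A two-sided 1:1 comparison would need 235 per arm. Then 137 × 1.10 = 150.7, so 151 per arm and 453 in total. Equal arms are therefore built into the stated sample size.

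**2. Effect of the asleep-arm restriction.** Let s be the share of speech-eloquent tumours (not given; 20%, 40% and 60% assumed), and let choice be spread evenly over the permitted arms. Expected asleep patients = 453 × (1 − s)/3, with the rest split equally:

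| s | Asleep | Each other arm | Share of remaining patients needed in asleep arm for 1:1:1, (1/3)/(1 − s) |
|---|---|---|---|
| 20% | 121 | 166 | 42% |
| 40% | 91 | 181 | 56% |
| 60% | 60 | 196 | 83% |

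Above s = 2/3, a 1:1:1 split is impossible without turning patients away. The last column treats every tumour that is not speech-eloquent as open to asleep mapping. Study design says this only of motor-eloquent tumours, while the inclusion criteria also admit sensory and visual areas.

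**3. If full arms were closed.** With share q for the least-used technique, 151/q consecutive patients are needed before that arm reaches 151. If the other two arms also stop at 151, the fraction not enrolled is 1 − 453/(151/q) = 1 − 3q:

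| q (assumed) | Patients needed | Not enrolled |
|---|---|---|
| 25% | 604 | 151 (25%) |
| 20% | 755 | 302 (40%) |
| 10% | 1,510 | 1,057 (70%) |

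For an assumed mix of 45% awake, 20% asleep and 35% none, the awake arm fills near patient 151/0.45 ≈ 336. About 1 − 336/755 ≈ 56% of asleep patients would then come after it closed.

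**4. What unequal arms cost.** Standard error (SE) of the difference at 10% versus 3% = √(0.09/n for no mapping + 0.0291/n for mapping), with 411 evaluable patients:

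- 137:137 gives √(0.1191/137) = 0.0295, or 2.9 points.
- No mapping 144 (35%), asleep 82 (20%): √(0.000625 + 0.000355) = 0.0313, or 3.1 points.
- No mapping 144, asleep 41 (10%): √(0.000625 + 0.000710) = 0.0365, or 3.7 points.

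For the pooled comparison that reproduces 411, what matters is the size of the no-mapping arm: 137 versus 274 gives √(0.000657 + 0.000106) = 0.0276, or 2.8 points. If no mapping were the rare technique, 41 versus 370 gives √(0.002195 + 0.000079) = 0.0477, or 4.8 points.

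**The case against.** The strongest reply is that 1:1:1 is only a recruitment target. The study is open to additional centres, and asleep mapping is described through two centre-specific protocols. The mix of centres could therefore bring the totals near 151 per arm without steering any patient, and approximate balance could also arise by chance. This stands against any claim that the statements are strictly incompatible, or that sites must steer patients or stop enrolling consecutively. It does not settle the point: the article describes no such route, and it would mix arm with centre.

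A reader might infer from Data collection that staff assign the operation, making this an interventional study without safety oversight. The documents do not support that. The phrase stands beside data entry in a section on data capture and may mean only recording the arm. The recorded surgeon's rationale and the care-as-usual statement point to clinical choice. Nor do the leftover minimisation factors show hidden assignment, since randomisation is expressly denied. The oversight concern is conditional on the ratio being enforced through choice of technique.

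Three further points stand in part. The word consecutive appears only in the abstract; the body speaks of eligible patients. The article admits that the observational design leaves bias and does not present the ratio as evidence of comparability. An article may leave recruitment management to the full protocol, but what is at issue here is a ratio stated outright beside text it does not fit.

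**Conclusion.** The point holds as an unreconciled statement in the plan. Under usual-care choice the ratio is an outcome of practice and cannot be guaranteed together with consecutive enrolment; the documents do not show that the three could never coincide.

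Its size cannot be fixed from the documents, which give neither technique shares nor the speech-eloquent share. The 755-patient and 40% figures illustrate one assumed mix under an arm-closure rule that the article does not contain, and should not be read as a forecast. Over assumed shares of 25% to 10% the requirement runs from 604 to 1,510 patients. The precision given up by dropping the ratio is small under a moderate imbalance (2.9 to 3.1 points for asleep against none), but not always small: 3.7 points if asleep falls to 10%, and more if no mapping is the rare arm.

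The text should be changed, because enforcing the ratio by steering patients or closing arms would bias the comparison, whereas a planning target would not.

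**What to change.** Reconcile the abstract, Study design, Data collection and Study monitoring:

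- Replace the 1:1:1 ratio in the abstract and Study design with a planning target of about 151 per arm.
- State that the technique is decided in usual care, independently of enrolment; that each centre enrols all consenting eligible patients consecutively for whichever techniques it uses; and that no arm is closed early.
- Reword group allocation in Data collection as recording of the arm, if that is what is meant. If the sponsor does intend some mechanism for balancing the arms, describe it and reconcile it with the care-as-usual statement.
- Restate the power in Sample size for a range of arm splits, including cases where asleep mapping or no mapping is the smallest arm.

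A screening log per centre, with technique and reason for non-enrolment, would let readers check that enrolment was consecutive.

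The cost is wording, a short set of power figures and, if adopted, the log. The downside to state openly is that arms may be unequal, with a wider interval for comparisons involving the smallest arm.

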### Inclusion criteria

In order to be eligible to participate in this study, a subject must meet all of the following criteria:

Age ≥18 years and ≤90 years.Tumour diagnosed as HGG (WHO grade III/IV) on MRI as assessed by the neurosurgeon.Tumours situated in or near eloquent areas; motor cortex, sensory cortex, subcortical pyramidal tract, speech areas or visual areas as indicated on MRI (Sawaya grading II and II).^19^The tumour is suitable for resection (according to neurosurgeon).Written informed consent.

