### Primary study parameters

The primary endpoints will be analysed using multivariate logistic regression. Subgroup analyses for tumour grade (WHO grade III/IV), preoperative neurological morbidity, preoperative tumour volume, patient’s age (in 10-year age brackets) and tumour location/eloquence will be performed.

We will be including a stratification factor in the primary analysis model with each 10 observed events using the order of prognostic value as mentioned in the paragraph above, where the first 10 events will be used to estimate the effect of the arm. This rule will be applied in case less than 40 patients in total develop neurological deterioration. In the so constructed multivariate logistic regression model the treatment arm effect will be tested at 4% significance level. The primary analysis of proportion of patients without residual contrast-enhancing and non-contrast-enhancing tumour consist of a multivariate logistic regression, where arm effect is corrected for all minimisation factors. In this model the group effect will be tested at 1% significance level. Manual or semiautomatic segmentation will be performed on axial T1 and T2/FLAIR MRI contrast enhanced slices to measure preoperative and postoperative tumour volume. A determination of volumes will be calculated blinded for the treatment group.

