## Discussion

Neurosurgeons face a major dilemma during glioma surgery: maximising extent of resection while minimising risk of postoperative neurological deficits. The use of awake or asleep mapping techniques has the potential to equip the surgeon intraoperatively with the needed information to balance these two surgical goals.

A substantial amount of evidence is available on the usefulness of awake mapping to increase resection percentage while preserving quality of life in LGG patients.^23–34^ In contrast, only very few studies have reported the use of awake mapping in HGG patients, although this technique could be of important value in these patients as well.^17 23 25–27 34^ Recent retrospective evidence showed that glioblastoma patients operated with awake mapping had significant less postoperative neurological morbidity and significantly higher percentage of total resections.^35 36^ In patients with motor-eloquent tumours, the use of asleep mapping techniques with evoked potentials or CDM can be a viable alternative to preserve these functional tracts.^20 37 38^

There is a clear need for solid prospective evidence of the use of these techniques in HGG patients. The presented international neurosurgical research consortium will provide the needed infrastructure to perform ongoing large-scale data collection.^18^ This study aims to evaluate whether the use of awake or asleep mapping is the appropriate answer to the surgeon’s surgical dilemma during HGG resections. Furthermore, it will be the first to directly compare awake and asleep mapping techniques in their ability to improve patient outcomes for neurological morbidity, quality of life and survival. Last, using various multivariate analyses, there will be an additional focus on identifying the best surgical choice in subgroups of HGG patients.

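### Speech-eloquent tumours are kept out of the asleep arm, but the primary and survival models compare the arms over all patients and in practice do not adjust for tumour location

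*Protocol article*

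**What the plan says.** All statements are in the Protocol article.

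- **Who can enter which arm.** Study design: "Patients with motor-eloquent tumours will be treated in all study arms", whereas "speech-eloquent tumours will only be treated in either the awake mapping or no mapping arm". The Introduction gives the technical reason: "speech mapping can only be performed when the patient is awake".
- **One eligible population.** The Inclusion criteria are common to all arms and cover "motor cortex, sensory cortex, subcortical pyramidal tract, speech areas or visual areas as indicated on MRI".
- **Ratio.** Study design: "Eligible patients are operated using awake mapping, asleep mapping or no mapping with a 1:1:1 ratio". The Abstract says the same of consecutive patients.
- **Sample size.** One control rate (10% deterioration) and one rate for both mapping arms (3%), with 411 patients, 137 per arm. For residual tumour the rates are 25% and 50%.
- **Analysis population.** Data analysis takes all eligible patients by intention to treat and makes no restriction by location.
- **NIHSS model.** Primary study parameters lists grade, preoperative morbidity, preoperative volume, age and, last, location/eloquence, both as subgroups and as the order in which factors enter. With fewer than 40 deteriorations in total, the first 10 events are spent on arm and each further 10 admit one factor. Then: "In the so constructed multivariate logistic regression model the treatment arm effect will be tested at 4% significance level".
- **Residual-tumour model.** Arm is corrected for the minimisation factors and tested at 1%. The only list of these, under Secondary study parameters for PFS and OS, is age group, KPS and hemisphere.
- **Purpose.** Discussion: "it will be the first to directly compare awake and asleep mapping techniques".

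**The concern.** The arms differ in tumour location by construction, not by chance or by surgeon preference. If location bears on deterioration, resectability or survival, an asleep-versus-none or asleep-versus-awake difference over all patients is partly a difference between motor-eloquent and mixed case series. The article treats location as prognostic, since it places it in a list ordered by prognostic value.

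The imbalance would matter little if the models adjusted for location, but the stated rules leave it out. The comparison of the two mapping techniques, which the Discussion presents as the study's novelty, is directly exposed. So is the pooled comparison of mapping with no mapping, because half of the mapping group is asleep.

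**Working it through.** **1. The plan's own figure.** Inputs from Sample size: p1 = 0.10, p2 = 0.03, 80% power, 4% level, continuity correction. With k = 2 mapping patients per control and a one-sided test (z = 1.751 and 0.842), the pooled proportion is p̄ = (0.10 + 2×0.03)/3 = 0.0533.

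n = [1.751·√(1.5·p̄(1−p̄)) + 0.842·√(0.09 + 0.0291/2)]² / 0.07² = 116 controls.

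Continuity correction: (116/4)·[1 + √(1 + 2·3/(116·2·0.07))]² = 137 controls, plus 274 mapping patients = 411.

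This matches the plan exactly. Two-sided 2:1 with correction gives 492, and 1:1 with correction gives 194 (one-sided) or 235 (two-sided) per arm. So 411 treats awake and asleep as one mapping group against all controls.

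**2. Does location enter the NIHSS model?** Expected events at the design rates: 137 × (0.10 + 0.03 + 0.03) = 21.9. The probability of 40 or more is 0.0002, so the event rule applies. Ten events go to arm and the next ten admit grade. Location, fifth, needs 10 + 5×10 = 60 events. Since the rule operates only below 40, location can never enter while it operates.

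**3. Does it enter the other models?** The residual-tumour, PFS and OS models use age, KPS and hemisphere. Hemisphere is only a partial stand-in for speech location.

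**4. Size of the bias (assumed inputs).** Let s be the share of controls with speech-eloquent tumours (20–50%) and r the speech:motor risk ratio (0.5–2). Control rate 10%, no mapping effect in either tumour class.

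- Motor risk, which is the asleep rate: 0.10/(1 − s + s·r).
- False difference, none minus asleep: 0.10 minus that rate.
- Rejection: unadjusted test, 137 v 137, two-sided 4%, normal approximation.

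| s | r | Asleep rate | False difference (points) | Rejection |
|---|---|---|---|---|
| 20% | 0.5 | 11.1% | −1.1 | 4.9% |
| 20% | 2 | 8.3% | +1.7 | 6.3% |
| 30% | 0.5 | 11.8% | −1.8 | 6.2% |
| 30% | 2 | 7.7% | +2.3 | 8.7% |
| 50% | 0.5 | 13.3% | −3.3 | 11.8% |
| 50% | 2 | 6.7% | +3.3 | 14.6% |

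If awake has the same speech share as control, the pooled mapping rate is the mean of the asleep rate and 10%. The false difference then halves, to at most 1.7 points.

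**5. The same shift at the design rates.** If asleep shows 3% and all controls 10%, motor-eloquent controls lie between 6.7% and 13.3% under the same assumptions. An apparent 7-point gain then corresponds to 6.7 − 3 = 3.7 up to 13.3 − 3 = 10.3 points among comparable patients.

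**6. Power on comparable patients.** Motor-eloquent controls number 137(1 − s). Asleep is taken as 137. Continuity-corrected tests.

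| s | Motor controls | NIHSS, 4% one-sided | NIHSS, 4% two-sided | Residual tumour, 1% two-sided |
|---|---|---|---|---|
| 0 | 137 | 64% | 52% | 95% |
| 20% | 110 | 60% | 49% | 91% |
| 30% | 96 | 57% | 46% | 88% |
| 40% | 82 | 54% | 44% | 84% |
| 50% | 68 | 51% | 41% | 77% |

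**The case against.** - **A location subgroup is planned.** This stands. Its motor-eloquent stratum is free of this particular confounding, so a reader who concludes that every asleep contrast in the study is confounded goes too far. But the subgroup does not carry the 4% or 1% test.
- **Adjustment would work.** A reader might infer that no regression could repair the imbalance, because no speech-eloquent patient receives asleep mapping. That is too strong. Motor-eloquent patients appear in all arms, so the asleep effect is estimable there. With no mapping effect and only a location effect, a model with arm and location returns an asleep-versus-none odds ratio of exactly 1.00. What remains out of reach is an asleep effect in speech-eloquent patients, which nobody claims. Bias after adjustment would need a further assumption, such as an awake effect that differs by location. The fault is that location is left out.
- **The event rule may not bite under the null.** Partly right. With no mapping effect, expected events are 137 × (0.10 + 0.10 + 0.067) = 36.5 up to 137 × (0.10 + 0.10 + 0.133) = 45.7 at the extremes of step 4, on either side of 40. At 40 or more, the natural reading is that all factors enter, though the article does not say so. The rejection figures therefore describe a comparison without location. At the design rates, and in the residual-tumour and survival models, this escape is absent.
- **Larger figures depend on chosen inputs.** With half of controls speech-eloquent and risks of 5% (motor) and 15% (speech), the false difference is 5 points and rejection 31%. The documents support neither input. For the pooled contrast this case falls to 2.5 points and about 13%. Reversing the risks implies 137 × (0.15 + 0.10 + 0.10) = 48 events, so the rule would usually not apply.
- **The 1:1:1 ratio.** A reader might infer that it is impossible. The article states it overall, and an overall ratio can be met by numbers enrolled. It cannot hold within the speech-eloquent stratum, but the article does not say that it does.
- **Bias is acknowledged as a limitation of the observational design.** That is a general remark. This imbalance is known in advance and removable in the analysis.

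**Conclusion.** The point holds. The exclusion is explicit, and the model rules in the article leave location out of the primary NIHSS analysis at the design rates and out of the residual-tumour, PFS and OS models altogether. The primary asleep-versus-none and asleep-versus-awake contrasts and the adjusted survival contrasts mix technique with tumour location. The pooled mapping contrast does so at about half the size.

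Under the stated assumptions (20–50% of controls speech-eloquent, risk ratio 0.5–2, control rate 10%), the NIHSS asleep-versus-none difference is shifted by up to 3.3 points either way against a planned 7. An unadjusted nominal 4% test rejects in about 5–15% of trials with no mapping effect. The direction cannot be known from the documents, so the bias cannot be called conservative. That the arms are unequal in location needs no assumption; the size does.

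**What to change.** 1. Make motor-eloquent patients the primary population for every contrast that involves the asleep arm, for both primary endpoints, PFS and OS.
2. Force motor/speech location into the awake-versus-none and pooled mapping-versus-none models for the same four outcomes, ahead of the event-limited factors.
3. Restate the power of the asleep contrasts on the motor-eloquent subset, with the assumed speech share shown: for example 110 to 68 comparable controls if 20–50% are speech-eloquent.
4. Keep the 1:1:1 ratio if wanted, but describe it as overall and not within location.
5. State how sensory and visual tumours are classed for these analyses. They are eligible, but Study design does not say which arms take them.

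No new data are needed, because the baseline case report form already records eloquent areas. The cost is fewer patients and lower stated power for the asleep contrasts. The NIHSS power for asleep versus none is already only 64% one-sided (52% two-sided) with all 137 controls, because 411 was sized on the pooled mapping group.
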